# A family-centered lifestyle intervention to improve body composition and bone mass in overweight and obese children 6 through 8 years: a randomized controlled trial study protocol

**DOI:** 10.1186/1471-2458-13-383

**Published:** 2013-04-25

**Keywords:** Childhood obesity, Lifestyle interventions, Body composition, Bone, Dairy, Family-centered

## Abstract

**Background:**

Childhood obesity gives rise to health complications including impaired musculoskeletal development that associates with increased risk of fractures. Prevention and treatment programs should focus on nutrition education, increasing physical activity (PA), reducing sedentary behaviours, and should monitor bone mass as a component of body composition. To ensure lifestyle changes are sustained in the home environment, programs need to be family-centered. To date, no study has reported on a family-centered lifestyle intervention for obese children that aims to not only ameliorate adiposity, but also support increases in bone and lean muscle mass. Furthermore, it is unknown if programs of such nature can also favorably change eating and activity behaviors. The aim of this study is to determine the effects of a 1 y family-centered lifestyle intervention, focused on both nutrient dense foods including increased intakes of milk and alternatives, plus total and weight-bearing PA, on body composition and bone mass in overweight or obese children.

**Methods/design:**

The study design is a randomized controlled trial for overweight or obese children (6–8 y). Participants are randomized to control, standard treatment (StTx) or modified treatment (ModTx). This study is family-centred and includes individualized counselling sessions on nutrition, PA and sedentary behaviors occurring 4 weeks after baseline for 5 months, then at the end of month 8. The control group receives counselling at the end of the study. All groups are measured at baseline and every 3 months for the primary outcome of changes in body mass index Z-scores. At each visit blood is drawn and children complete a researcher-administered behavior questionnaire and muscle function testing. Changes from baseline to 12 months in body fat (% and mass), waist circumference, lean body mass, bone (mineral content, mineral density, size and volumetric density), dietary intake, self-reported PA and sedentary behaviour are examined.

**Discussion:**

This family-centered theory-based study permits for biochemical and physiological assessments. This trial will assess the effectiveness of the intervention at changing lifestyle behaviours by decreasing adiposity while enhancing lean and bone mass. If successful, the intervention proposed offers new insights for the management or treatment of childhood obesity.

**Trial registration:**

ClinicalTrials.gov, NCT01290016.

## Background

Childhood obesity is a worldwide problem with immediate and long-term health consequences [1,2]. Not only are obese children at a greater risk of developing medical complications that include cardiovascular disease, type 2 diabetes, hypertension and lipid disorders [2], they are also at risk for developing low self esteem and often experience psychological distress [3]. Furthermore, it is reported that obese children may also present with orthopaedic and bone-related problems, including lower bone mass for their body weight [4,5], reduced bone strength [6] and increased risk of bone fractures [6,7].

Modifiable determinants of childhood obesity include energy intake (diet) and energy expenditure (physical activity (PA) and inactivity); these two components typically form the basis of prevention and treatment programs. Health Canada’s strategy to reduce childhood obesity addresses these two components, encouraging children to follow Canada’s Food Guide (CFG) [8] and participate in daily moderate to vigorous cardiovascular PA for 60-minutes per day [9]. Despite public health initiatives, statistics show that 1 in 5 Canadian children have energy intakes that exceed their energy expenditure [10]. Although children exceed their energy intakes, 71%, 37%, and 27% of children 4 to 8 y are not meeting the recommended servings of vegetables and fruit, milk and alternatives, and cereal products, respectively, per day [10]. Furthermore, only 9% of boys and 4% of Canadian girls accumulate 60 minutes of moderate-to-vigorous PA on at least 6 days a week, averaging 8.6 hours per day, or 62%, of their waking hours being sedentary [11].

Interventions involving overweight or obese children should address the modifiable behaviors of obesity together, including discussions about both diet and physical activity [12,13]. They should also be “family-centered” with at least one parent involved in the program [14]. The Transtheoretical Model (TTM) allows for assessment of participant awareness and acceptance of the obesity problem including their desires to change behaviors [15]. Applying TTM in programs can be accomplished through different interviewing techniques and counseling strategies in order to achieve individual goals [16]. Interventions should be sensitive to culture and socioeconomic status, as specific population groups may differ in terms of cultural needs and realistic lifestyle changes [17]. In addition, programs should to be tailored and include strategies such as goal setting [18], and educational sessions conducted by health professionals who deliver short and simple messages [19].

It is important that intervention programs start young, as health consequences can carry throughout adolescences to [1,2]. Programs targeting childhood obesity have been published using different study designs and interventions, making it is difficult to determine if the effects of the interventions favourably change body mass index (BMI) Z-scores and adiposity (fat mass) [20,21]. Musculoskeletal health of obese children has also been examined, showing that despite having higher bone mineral density (BMD) and bone size [4,5], obese children are at an increased risk of facture [22,23]. Studies assessing bone geometry and strength propose that the bones are not as “developed” and that the extra weight (fat mass) negatively effects bone [23]. The muscle-system is important for cortical bone health [24] and despite having elevated BMD, the increased weight on the cortical mass may be too high, thereby leading to increased fractures [22,23]. Furthermore, bone adapts to dynamic forces of muscle contractions, not by static forces of fat mass [25].

Research that has studied bone health in children uses different methodology techniques for assessing bone [22,25,26]. Recent studies that have use both dual-energy X-ray absorptiometry (DXA) and peripheral quantitative computed tomography (pQCT) allow for assessment of volumetric BMD (vBMD) (g/cm^3^) and bone geometry and not exclusively area BMD (aBMD) by DXA [22]. This has allowed for the discovery of negative relation to cortical and trabecular vBMD in obese children [27]. The relationship between bone and obesity also extends to environmental behaviors, including physical activity and nutrition [28]; research suggests that low circulating 25-hydroxyvitamin D (25(OH)D) concentrations [29-31] due to decreased sun exposure from sedentary lifestyles [32], poor diet [29], and increased vitamin D storage as it sequesters in adipose tissue [33,34]. Studies have attempted to enhance bone mass in children using dairy foods [35-37] or calcium supplements [38-41]. Doubling of calcium intake (from 750 mg/d to 1600 mg/d) in non-obese children enhanced bone density by 18.8% [42], suggesting a possible role for higher milk (calcium and vitamin D) intakes in improving bone health [43]. In addition to increased calcium intake, adding weight-bearing PA improves bone mass [44] and whole body bone mineral density (WB-BMD) [45].

Despite the well established role for calcium and milk in developing healthy bone mass, the contribution of milk and alternatives (i.e. cheese, yogurt, cottage cheese, soy beverages) and/or calcium achieving or maintaining healthy body weight is less clear [46-49]. Reviews that aim to conclude if increased dairy or calcium intakes affect body weight report mixed evidence [47,50]. To date no study has evaluated the effects of increased milk and alternatives plus total and weight-bearing PA on body composition and indices of bone health in prepubescent children, using a family-centered lifestyle intervention encompassing both education and behavioral modifying techniques. A study that assesses bone and body composition in addition to biomarkers of bone and obesity in overweight/ obese children who participate in a lifestyle intervention by both DXA and pQCT is warranted [27].

To our knowledge, there is no study that has examined the effects of a family-centered lifestyle intervention that investigated the altered bone structure [51] or modulators of bone health in addition to those that can reduce adiposity [52]. This paper shares a comprehensive approach that will be used in a randomized controlled trial of a 1-y lifestyle intervention in overweight and obese prepubescent children. This study will involve two levels of intervention: one focused on meeting recommended age-specific targets for nutrition and physical activity (standard intervention [StTx]) and a second focused on increased milk and alternatives consumption and weight-bearing activities (modified intervention [ModTx]) as a means to enhance support for bone mass. It is hypothesized that children receiving the ModTx will have a lower BMI Z-score, lower waist circumference and improved weight-for-age Z-score and increased bone mass and strength at 12-months compared to children in the StTx and control groups. Secondary objectives are to examine the effects of the intervention on changes of children’s eating behaviour throughout the intervention compared to control.

This study, the McGill Youth Lifestyle Intervention for Food and Exercise (MY LIFE Study), embraces the family-centered approach in a non-institutional setting. The primary focus of the MY LIFE Study is to create realistic nutrition and PA goals, while providing families with the necessary education and behavioral tools necessary to help the child meet their immediate and long-term goals of attaining a healthy lifestyle.

The study methods are in accordance with the CONSORT guidelines for reporting randomized trials [53]. Ethical approvals were obtained from McGill University Faculty of Medicine Institutional Review Board and Montreal Public School Boards. The MY LIFE Study is registered online at http://www.Clinicaltrials.gov (Trial # NCT01290016).

## Methods/design

### Participants

Eligible participants are healthy children 6–8 y, living in or near Montréal, Québec, who are overweight or obese according to the World Health Organization weight-for-height BMI cut-off criteria [54]. In addition to parental consent, participants provide written informed assent by reading and signing an assent form written at the grade 1 level. Participants must be either English or French. Only one eligible child per household is included in the study. Exclusion criteria includes: 1) known or suspected serious, chronic illness of childhood, such as cancer, Crohn’s disease, nephrotic syndrome, rheumatic conditions, and diabetes, etc., or those with disturbances in bone, vitamin D or mineral ion metabolism including rickets, osteomalacia, liver disease, renal disease, immobilization (complete or partial), current fractures, and disorders of the parathyroid gland; 2) use in the past 3 months, medications known to affect bone and/or mineral ion metabolism including all glucocorticoids, phosphate therapy or vitamin D analogues and any bisphosphonates; 3) severe anemia precluding blood sampling (previously diagnosed); 4) established diabetes mellitus (any type) and 5) hyperlipidemia ascribed to non-dietary causes.

### Recruitment strategy

Participants are recruited through public and private elementary schools (kindergarten through grade 3), primary healthcare organizations including physician referrals, word of mouth and local advertisements through newspaper, internet, radio commercials and postal mailings. Recruitment in schools included placing a bilingual study brochure in the children’s homework folders. Due to the sensitivity of the topic, all brochures are placed in envelopes addressed “To the Parents/ Pour les parents”. Interested participants contacted the research team by electronic mail or telephone. Participants are screened for eligibility by a researcher during the initial telephone call. If eligible, the family is scheduled for a baseline assessment within three weeks of the screening call at the research unit.

### Outcomes

The primary outcome of this study is change in BMI Z-score from baseline to 12 months. Secondary outcome measures include changes in body weight (kg), waist circumference (cm), % body fat (%), lean body mass (g), BMD (g) and bone mineral content (BMC: g), architecture of bone (radius and tibia) as well as bone strength. Changes in food intake, PA and average time spent engaging in sedentary activity (minutes/day) are also assessed. Other outcomes include changes in eating behaviour and child’s perceptions of healthy nutrition and physical activity behaviours.

### Randomization and blinding

Children are randomized by a computer-generated list using stratified block randomization of three per block to maintain balance. Two stratification factors are implemented: gender and BMI (overweight and obese). In order to maintain blinding for non-intervention related measurements, children are randomized to control, StTx or ModTx groups by the registered dietitian who conducts the interventions. Participants are informed of their group at the end of their baseline visit. All other research staff are blinded.

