### Baseline

All participants arrive at the research unit fasted for 12-hours. Child assent and parent consent are obtained. Child’s weight and height are measured to confirm BMI criteria are met. All children are tested for normal blood glucose using a glucometer; those with blood glucose above ≥ 6.9 mmol/L are advised to seek subsequent medical assessment and are not enrolled in the study. Those with a normal blood glucose value (< 6.9 mmol/L) have a 9 ml blood sample taken. Parents complete a socio-demographic questionnaire and with a researcher, the child answers a series of questions from a study-specific questionnaire (*Child Intention Questionnaire* (CIQ)). All families receive a general nutrition and PA educational session by a registered dietitian. Parents are instructed how to complete a 3-day food diary; they are provided with a pre-paid envelope and asked to mail the diary once completed. The food diary will capture 3 non-consecutive days including one weekend day. At the end of the baseline visit, children choose from a ball, ball and racket or jumping rope, as a part of remuneration for their time with the dual purpose to encourage physical activity. Parents are told which group they are in and schedule their next visit.

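### The dietitian who delivers the intervention randomises children in blocks of three, so about one assignment in three is predictable to that person

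*Protocol article*

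**What the plan says.** The protocol article, section Randomization and blinding, fixes the method: "Children are randomized by a computer-generated list using stratified block randomization of three per block to maintain balance". It adds: "Two stratification factors are implemented: gender and BMI (overweight and obese", which makes four strata. The person who allocates is named: "children are randomized to control, StTx or ModTx groups by the registered dietitian who conducts the interventions". The reason given is "In order to maintain blinding for non-intervention related measurements". The same section states "All other research staff are blinded" and "Participants are informed of their group at the end of their baseline visit".

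The section Baseline adds that "All families receive a general nutrition and PA educational session by a registered dietitian". In that section's account of the visit, this session comes before parents learn the group. The section Recruitment strategy has a researcher, not the dietitian, screen families by telephone.

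**The concern.** Concealment protects the step before assignment: nobody who can influence entry or baseline contact should be able to foresee the next arm. Here the allocator is the interventionist, who cannot be blinded to past assignments and has a natural interest in the result. The single block size stated equals the number of arms, so once two children in a block are placed, the third follows.

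The stated reason concerns a different safeguard. Keeping assessors blinded after assignment requires only that they are not told the arm. It does not require the counsellor to be the one who randomises.

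If foreknowledge influenced which families entered, or how they were handled at baseline, the arms could differ in motivation. Adjusting for measured baseline variables would correct that only in part, and the comparison of BMI Z-score change would be affected.

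**Working it through.** **Inputs**
- Arms: 3 (control, StTx, ModTx). Block size: 3. Strata: 2 × 2 = 4. All from Randomization and blinding.
- Total: 39 per arm, from Sample size calculation.
- Assumption: the allocator knows the block size and all earlier assignments in the stratum, but cannot see the list.

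**The plan's sample size**, used here only to count blocks. For a difference of 0.2, SD 0.3, two-sided 5% and 80% power:
- n per arm = 2 × (0.3 × (1.960 + 0.842) / 0.2)² = 35.3.
- With 10% drop-out: 35.3 / 0.9 = 39.2, so 39 per arm and 3 × 39 = 117. The section also gives 116; the difference of one is immaterial here.

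**Predictability within one block of three**
- First child: three arms open, best guess right with probability 1/3.
- Second child: two arms open, 1/2.
- Third child: one arm left, 1.
- Average: (1/3 + 1/2 + 1) / 3 = 0.611. With full concealment it would be 1/3 = 0.333.

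**Number of fully determined assignments**
- Each complete block has one. If all four strata end on a complete block: 117 / 3 = 39.
- Otherwise each stratum may end with 1 or 2 children in an open block. The four remainders must sum to a multiple of 3, because 117 is one, and cannot exceed 4 × 2 = 8. The possible sums are therefore 0, 3 and 6.
- Complete blocks: 117/3 = 39, 114/3 = 38 or 111/3 = 37. So 37 to 39 children, or 32% to 33% of 117.

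**Would larger blocks alone be enough?** Take fixed blocks of six, two per arm, and the same observer.
- Certain assignments: the sixth always, and the fifth when the two remaining places belong to the same arm (probability 1/5). (1 + 1/5) / 6 = 20%.
- Best-guess probability by position: 1/3, 2/5, 1/2, 8/15, 3/5, 1. The sum is 3.367, and 3.367 / 6 = 0.561.

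| Scheme | Certain | Best guess |
|---|---|---|
| Fixed blocks of 3 (as planned) | 33.3% | 61.1% |
| Fixed blocks of 6 | 20.0% | 56.1% |
| Simple randomisation | 0% | 33.3% |

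Doubling the block size lowers the best-guess rate by only five percentage points.

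**The case against.** The strongest reply is that predictability is not bias, and that the article closes most routes from one to the other.
- A researcher screens by telephone, and visits are arranged to suit the family. Nothing says that the dietitian books baseline visits or obtains consent.
- The child's stratum depends on overweight or obese class. Weight and height are measured to confirm the BMI criteria only at the baseline visit, so before then the relevant block position can be anticipated only by guessing that class.
- The entry checks at the visit, BMI and glucose, are objective.
- The primary outcome is a measured quantity, other research staff are blinded, and the analysis section provides for adjustment of baseline imbalances.

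All of this stands, and it narrows the opportunity. It does not make the sequence unpredictable to the allocator.

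A reader might go further and infer three things that the text does not support:
- **That the dietitian can read the list, so that every assignment is known.** The article does not say who holds the list or how an assignment is released. A condensed article may leave that to the full protocol, and sealed envelopes would fit the text equally well. The calculation above does not depend on it.
- **That the allocator shapes the baseline education according to the coming arm.** The article speaks of a dietitian at baseline and follow-up visits, and of dietitians in the plural in the Discussion. It does not confirm that this is the same person. Note g to Table 1 describes the session as a basic review.
- **That the arrangement causes performance bias.** A counsellor knows the arm once counselling begins, whoever randomises. That is inherent in the design and would remain after any change to allocation.

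**Conclusion.** The point holds as one of predictability. As described, 37 to 39 of 117 assignments can be deduced in advance by the person who makes them and then delivers the intervention, and that person's average best-guess rate is 61% against 33% by chance. This assumes that the allocator is aware of the block size and that the size is constant, which is inferred from the single size stated: "using stratified block randomization of three per block to maintain balance". It does not assume sight of the list.

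Selection through enrolment or baseline contact is possible but not shown. The documents give no basis for estimating an effect on the BMI Z-score comparison, and none is claimed. They do not support saying that allocation is openly known or that the result is biased. The change is still worth making: the weakness is in the method as stated, the reason given for it does not require it, and the remedy is cheap.

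**What to change.** For children not yet randomised:
1. Have an existing team member without family contact generate and hold the list.
2. Mix block sizes at random within strata, for example 3 and 6, and do not disclose them to the dietitian.
3. Release each assignment to the dietitian only after consent, confirmed eligibility, baseline measurements and the common education session are complete.

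The dietitian can still be the only staff member who learns the arm, so assessors stay blinded. The elements belong together, since larger blocks alone leave much of the predictability in place.

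The cost is a new list, a simple release procedure with minor administrative work, and slightly looser balance within small strata. The benefit depends on how many children remain. The article appeared in April 2013 and expects results in 2014 after 12 months of follow-up, so that number may be small. For children already randomised, the trial report should state who allocated, who held the list and what the allocator knew.

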### Study protocol

All assessments take place at the same research unit every 3 months (Table 1). Appointments are scheduled at the convenience of the family including weekend and evenings.

**Table 1 T1:** The MYLIFE study design: assessment and scheduling of baseline, follow-up visits and intervention sessions

	**Baseline**	**3-mo**			**6-mo**			**9-mo**			**12-mo**		
**Blood sampled **^**a**^	●	●			●			●			●		
**Anthropometry **^**b**^	●	●			●			●			●		

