### Follow-up visits

Children return to the clinic every 3-months for in the 12-h fasted state for blood sampling (Table 1). Parents complete a questionnaire about child’s eating behavior, physical activity level, and sun exposure. During these visits, blood tests, anthropometry, body composition, bone assessments, and muscle function tests are performed. The CIQ is also completed. A dietitian is present at all follow-up visits to ensure parents receive the same nutrition and physical activity advice throughout the study. We believe that families require continuous support and therefore having a dietitian present at all study visits helps reduce participant withdrawal, especially for the control group.

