### Measurements

#### Biochemistry

Immediately after blood is drawn, plasma samples are spun for 20-minutes. Serum samples are spun after 30 min, and used to measure insulin (0.5 ml) while plasma (0.5 ml) is used for measurement of glucose, liver enzymes (ALT, AST) and lipids (LDL, HDL, total cholesterol, TG and hormones) using autoanalzyers (Beckman Access and Beckman DxC600 CA, USA) at the Montreal Children’s Hospital (MCH) clinical chemistry laboratory (certified by the provincial quality assurance program, the Laboratoire de santé publique du QC). These samples are sent for analysis to the MCH within 4-hours of blood sampling. A pediatrician reviews all biochemical data; abnormal results are addressed on an individual basis to ensure children are healthy. These biochemical outcomes are in line with the 2006 Canadian clinical practice guidelines on the management and prevention of obesity in adults and children [55].

In addition to the recommended biochemistry, we will also examine in our research unit the following in the view of bone health outcomes and satiety. Vitamin D status is examined using plasma 25(OH)D concentration, as well as osteocalcin and PTH concentrations using an autoanalyzer (Liaison, DiaSorin, Ontario, Canada). Plasma is reserved to measure 1,25-dihydroxyvitamin D (1,25(OH)_2_D) as needed using LC-MS/MS (Warnex Bioanalytical Services, Quebec, Canada). Blood samples to analyze satiety markers are prepared by adding inhibitors (20 uL AEBSF and 20 uL DPP-4) to one 2 mL tube. Satiety markers are measured at McGill University using multiplex assays and luminex technology (EMD Millipore Corporation, Billerica, MA, USA): grehlin (acylated and nonacylated), GLP-1, neuropeptide YY, adiponectin and leptin. For red blood cell analysis, methanol-H_2_O-BHT is added in equivalent volume to red blood cell volume and spun. All CV% are <5% and typically 1 to 2%. HOMA-IR is calculated as the product of the fasting insulin (IU/ml) and plasma glucose (mmol/L)/22.5 [56].

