Nevertheless, counselling obese children poses unique challenges and barriers, including lack of overall family involvement, identifying participant motivation, support services, time and reimbursement [102]. Although including all family members in all sessions is important, it is true for some it may not benefit the child, particularly if parental level of support or willingness to change behaviour is not beneficial to the child [103]. A strength of the MY LIFE Study is the focus on the family environment and allows for sessions to be tailored to family needs. Our study offers continuous support to families by having dietitians available at all visits and conducting all follow-up visits at times that meet family needs. It is important that clinicians are capable of identifying behaviors that contribute to the child’s weight status and are able to work with the child to modify these behaviors [104]. The MY LIFE Study interventions are designed in a manner to support these needs, by using standard documentation techniques that utilize study tools (CEB-Q and PAQ-C) and still allow for variability of counselling topics. The MY LIFE Study provides an excellent example of how national educational tools, specifically the Canada’s Food Guide and Physical Activity Guide, can be used in a clinical setting. We believe that employing a family-centered approach that considers the family environment, developmental stage, as well as food and activity preferences will improve the program’s success. A focus on fun yet feasible activities will assist both children and parents in adhering to the program.

The results of the MY LIFE Study will be published in 2014 in relevant organizations and peer-reviewed academic journals. The study protocol presented in this paper is anticipated to help others who research the same area, and ultimately in creating treatment programs to combat childhood obesity.

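### Assessments may be booked in the evening, yet each one requires a 12-hour fasted blood draw, so an evening visit means a day-long fast or a non-fasted sample

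*Protocol article*

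**What the plan says.** **Timing.** The Study protocol section opens with "All assessments take place at the same research unit every 3 months (Table 1") and goes straight on to "Appointments are scheduled at the convenience of the family including weekend and evenings". The Discussion presents this flexibility as support for families and describes "conducting all follow-up visits at times that meet family needs".

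**Fasting.** The Baseline section states "All participants arrive at the research unit fasted for 12-hours". The Follow-up visits section states "Children return to the clinic every 3-months for in the 12-h fasted state for blood sampling".

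**Content of the visits.** The abstract says "At each visit blood is drawn", and Table 1 marks blood sampling at baseline, 3, 6, 9 and 12 months. The other measurements share these visits: "During these visits, blood tests, anthropometry, body composition, bone assessments, and muscle function tests are performed".

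**Use of the samples.** The Biochemistry section defines HOMA-IR from fasting insulin and glucose, and lists lipids (triglycerides among them) and a panel of satiety markers. The Baseline section turns away and refers children whose glucometer reading reaches 6.9 mmol/L. The Statistical analysis section compares biochemical indices between groups.

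**The concern.** One rule lets families choose an evening slot. The other demands 12 hours without food before the visit. For schoolchildren of 6 to 8 years the two cannot both hold in the evening without a fast that runs through the day. If the fast is not kept, the sample is treated as fasted when it is not.

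Three things are at stake:

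- **Fasting-based measures.** Glucose, insulin, HOMA-IR, triglycerides and satiety markers are interpreted as fasting values. A change score that sets a fasted sample against a fed one mixes feeding state with real change.
- **Enrolment.** A child who arrives fed at baseline could exceed the glucose limit because of a recent meal, and so be excluded and referred in error.
- **The children.** A family that follows both rules to the letter keeps the child from eating for most of the day before the draw and the jump tests. Nothing in the article suggests that this is intended.

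**Working it through.** **Step 1. Does the evening option cover the assessments?** The sentence just before it is about assessments, and the Discussion repeats flexible timing for all follow-up visits. The Discussion sentence does not mention evenings and does not cover baseline, so for baseline the reading rests on the Study protocol section alone. Nothing in the article confines fasted visits to mornings or separates the draw from an evening visit.

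**Step 2. Clock arithmetic.** Latest intake = visit time − 12 h.

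| Visit | Latest intake |
|---|---|
| 16:00 | 04:00 |
| 17:00 | 05:00 |
| 18:00 | 06:00 |
| 19:00 | 07:00 |
| 20:00 | 08:00 |

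The latest slots leave room for an early breakfast and nothing after it. By contrast, a last intake at 20:00 the evening before permits a visit from 08:00, so weekend mornings satisfy both rules.

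**Step 3. How a fed sample carries through.** HOMA-IR = insulin × glucose / 22.5. If feeding multiplies insulin by a and glucose by b, HOMA-IR is multiplied by a × b, with nothing to damp it. The documents give no values for a or b, nor the share of evening visits, so I put no figure on the total effect.

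**Step 4. Side check on the primary outcome.** Anthropometry is done at the same visits, so uncontrolled clock time could add noise to height and BMI Z-score.

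I first reproduced the plan's own figure from its inputs: difference 0.2, SD 0.3, 80% power, two-sided 5%.

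- n per arm = 2 × (1.960 + 0.842)² × (0.3/0.2)² = 35.3, rounded up to 36.
- With 10% dropout, 36/0.9 = 40 per arm, against 39 stated, which is close.
- 39 × 0.9 ≈ 35 completers per arm. Power = Φ(0.2/(0.3 × √(2/35)) − 1.96) = 79.6%.

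Now let s be an assumed SD of timing noise per BMI Z-score measurement, independent at the two ends of the change: SD = √(0.3² + 2s²).

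| s (assumed) | SD of change | Power, 35 per arm |
|---|---|---|
| 0 | 0.300 | 79.6% |
| 0.02 | 0.301 | 79.3% |
| 0.05 | 0.308 | 77.5% |
| 0.10 | 0.332 | 71.3% |
| 0.15 | 0.367 | 62.4% |

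The loss is small unless the noise is large. It is smaller still if the SD of 0.3 already contains some of this noise.

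**The case against.** The best defence is that the contradiction lies in the reading. Table 1 covers intervention sessions as well as assessments, and the six counselling sessions of 1.5 hours need no fast and suit evenings. The evening wording is permissive, the fast is mandatory, and staff may simply let the fast limit the slots. No sentence says that a fasted visit is actually held in the evening. A journal article also leaves clock windows and the handling of non-fasted samples to operating procedures or the analysis plan. Finally, the Outcomes section lists no blood marker as a primary, secondary or other outcome.

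Part of this stands. The text can be read more kindly, the absence of a time window is not in itself a fault, and the affected measures are not the main endpoints. But condensation excuses silence, not a printed permission that clashes with a printed requirement. The permission follows directly on a sentence about assessments. The affected measures do enter a planned group comparison, and the glucose reading decides enrolment.

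A reader might infer more than the documents support:

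- **Bias between arms.** Families learn their group only at the end of baseline, so baseline timing cannot depend on it. Counselling that overlaps study visits is placed at months 2, 5 and 8, after data collection; only a debriefing falls at 12 months. Nothing shows that measurement times differ by arm.
- **A large shift in BMI Z-score.** Assume a child of 125 cm with BMI 20, a height 0.5 to 1.0 cm lower in the evening, and 2.0 to 2.6 kg/m² per Z unit. A morning-to-evening switch then raises BMI by 20 × [(125/124.5)² − 1] = 0.16 to 20 × [(125/124)² − 1] = 0.32 kg/m², or about 0.06 to 0.16 Z. That is one child's shift on assumed figures and cannot be set against a group-mean target of 0.2. Even a 20-point difference between arms in the share of switchers, also assumed, would give only 0.20 × 0.06 = 0.012 to 0.20 × 0.16 = 0.032 Z.
- **Time-of-day variation in hormones and bone markers.** The documents give no figure or statement on it.
- **Laboratory transport.** The article says "These samples are sent for analysis to the MCH within 4-hours of blood sampling" but gives no laboratory hours, so no conflict with evening draws can be shown.

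**Conclusion.** The concern holds as a conflict between scheduling and fasting. As printed, the plan allows evening assessments and demands a 12-hour fast at all five of them. Each evening assessment then produces either a day-long fast or a sample unfit for the fasting-based indices and, at baseline, for the enrolment check. The arithmetic behind this needs no outside figure. How many samples are affected is unknown, because the share of evening assessments is not stated.

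The weight is moderate. The primary comparison is not threatened: clock time may add some noise to BMI Z-score, but the effect is minor and depends wholly on assumed values. The sample size needs no correction, and a claim of bias between arms is not supported. The point is still worth correcting, because the fault is in a stated rule and a few sentences would remove it.

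**What to change.** Reconcile the Study protocol section and the Discussion with the Baseline and Follow-up visits sections. The choice of rule belongs to the investigators. One consistent arrangement would be:

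- limit the evening option to counselling-only sessions, which need no fasted sample;
- book assessments with a fasted draw in the morning after an overnight fast, weekend mornings included;
- record the time of last intake and the time of the draw at each assessment;
- identify samples that miss the 12-hour fast and leave them out of HOMA-IR and the other fasting-based indices.

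On paper this is a change of wording and two recorded times. The real cost is less scheduling flexibility for families at five visits, partly offset by weekend mornings. It should be weighed against retention: with about 35 completers per arm the power is already 79.6%, so there is no margin for extra dropout.
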